### Study endpoints

The primary endpoint is the effect of oral vitamin D at 5,000 and 10,000 IU/day compared with placebo on the frequency of CD4 T-cell subsets and cytokine responses in peripheral blood mononuclear cells in patients with CIS and in healthy control participants at weeks 16 and 24 compared with baseline.

Secondary endpoints include: the following. 1) In the patients with CIS having MRI brain scans at baseline and week 24, the number of new and enlarging T2 lesions and gadolinium-enhancing lesions at week 24 compared with baseline in patients receiving oral vitamin D at 5000 IU and 10,000 IU/ day compared with placebo, 2) In the patients with CIS, the effects of oral vitamin D at 5,000 and 10,000 IU/day compared with placebo on relapse occurrence, calculated as the annualized relapse rate (ARR), the percentage of patients who are relapse-free, and time to first relapse. 3) The effects of oral vitamin D at 5,000 and 10,000 IU/day compared with placebo on the percentage of treated patients with CIS who are free from any evidence of disease (clinical and MRI) activity.

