### Study visits and outcome parameters

Participants will be screened following discussion of the trial and provision of signed, fully informed consent. If the participants satisfy the inclusion criteria at screening, they will then be scheduled for a baseline visit. The study scheme is outlined in Figure 1. There will be follow-up visits scheduled every 4 weeks visits until the end of study visit at week 24, and a safety visit at week 28 will also be arranged.

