**Figure 1 F1:**
[figure not shown]
**Schematic diagram of study structure.** There are two study groups of subjects: 39 healthy control participants and 45 patients with clinically isolated syndrome (CIS). Each of the two groups will be randomly allocated to one of three blinded treatments: placebo, vitamin D 5,000 IU, or vitamin D 10,000 IU daily. Study duration is 24 weeks with immunologic testing (primary endpoint) of all study participants at baseline, week 16, and week 24. There will be 4-weekly clinic visits to assess safety measures and clinical status. 4 weeks after completion of the study there will be a follow-up safety visit. Magnetic resonance imaging will be carried out at baseline and week 24 in the CIS population only.

At all visits, study participants will have any changes in medical history or medications recorded, and will undergo a general physical and neurologic examination. Patients with CIS will be assessed for any evidence of relapse, defined as the appearance of a new neurologic abnormality or reappearance of a previously seen neurologic abnormality, separated by at least 30 days from the onset of the preceding event. The abnormality must be present for at least 24 hours, must be based on objective clinical evidence, and must occur in the absence of fever or known infection.

Blood biochemistry, including liver function tests, electrolytes, urea, creatinine, and serum calcium will be measured at all study visits.

Serum vitamin D levels and parathormone levels will be assessed at baseline, and at weeks 4, 8, 12, 16 and 24. Serum 25(OH)D levels will be measured by liquid chromatography-mass spectrometry. Intact parathormone levels will be measured by a two-step sandwich immunoassay using chemiluminescence technology.

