Immunologic analysis will be carried out at baseline, and at weeks 16 and 24. Peripheral blood mononuclear cells (PBMCs) will be isolated within 12 hours of drawing blood, and cryopreserved until samples from all three time points have been collected. Cytokine production will be measured by ELISA, and will include 1) cytokine production by T cells and by other cells such as monocytes, and 2) flow cytometry, gating specifically on CD4 and CD8 T cells. 1) For analysis of PBMC cytokine production, PBMCs from each timepoint will be thawed out and stimulated with antigen (purified protein derivative (PPD) and tetanus toxoid) or polyclonal stimuli (anti-CD3 and phytohaemaglutinin). After 3 to 5 days (for polyclonal or antigen-specific stimulation respectively), the cell culture supernatants will be assayed by ELISA for cytokines including interleukin (IL)-10 and IL-17, and interferon (IFN)-γ. 1) For flow cytometry analysis of T-cell subsets, stimulated PBMCs from experiment 1, will be re-stimulated on day 5 with PMA and ionomycin in the presence of brefeldin A for 5 hours, followed by cell surface staining for T-cell markers (CD3, CD8) and intracellular staining for cytokines including IL-10, IL-17, and IFN-γ. The cells will be acquired on a FACSCanto II flow cytometer (Becton Dickinson), and analyzed using FlowJo software. Cytokine production by CD3+ CD8− (CD4 T-cells) and CD3+ CD8+ (CD8 T-cells) will be analyzed.

### *MRI scanning* at baseline visit and week 24

Brain MRI will be performed with contiguous axial 3 mm thick slices. Sequences will include axial and coronal T1-weighted spin echo (before and after gadolinium contrast enhancement), axial and sagittal PD/T2-weighted, and axial fast fluid attenuated inversion recovery, before contrast. MRI assessment will include 1) number of gadolinium enhancing lesions, 2) number of new and enlarging T2 lesions, and 3) the total number of new lesions (the sum of 1) and 2)).

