### Sample size

The power calculations for this study were based on a pilot study, which examined immunologic outcomes in four healthy control participants treated with vitamin D 5,000 to 10,000 IU/day at our institution [32]. All calculations for numbers needed in the study were based on α = 5% and β = 80%. Based on flow cytometry analysis of T-cell subsets, the change in IL-17-producing CD4 T-cells (Th17 cells) had an effect size (mean ± SD) of 1.9 ± 1.8 indicating a need for five study subjects per group for 80% power. For IFN-γ-producing CD4 T-cells (Th1 cells), the effect size was 4.3 ± 6.3) indicating a need for 19 subjects per group for 80% power. The changes noted in cytokines in response to anti-CD3 stimulation of PBMC were 1) for IL-17, Δ = 44.5 ± 44.3, thus 10 participants needed in each group; 2) for IFN-γ, Δ = 32.8 ± 1.2, thus 6 needed in each group; and 3) for IL-10, Δ = −455 ± 27, thus number needed is < 5. The changes noted in cytokines in response to PPD stimulation were 1) for IFN-γ, Δ = 1860 ± 1835, thus 10 needed, in each group and 2) for IL-10, Δ = −576 ± 86, thus number needed is <5. On the basis of these results, at least 10 subjects should be included in each group (the only immunologic endpoint not powered would be the flow cytometry analysis of the IFN-γ-producing cells). Recruiting 39 healthy controls and 45 patients with CIS will allow for a drop-out rate of 20% and 30% respectively.

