### Statistical methods

All analyses assume a two-sided test of hypothesis with an overall α level of 0.05. Immunologic endpoints and *post hoc* analyses, which will include the 16 and 24 week endpoints, are considered exploratory, and will not be adjusted for multiple comparisons. Descriptive statistics will be presented as mean ± SD. Non-parametric tests will be used to compare characteristics between treatment groups. For outcomes, the sign/sign rank test will be used to evaluate continuous outcomes. McNemar testing will be used to categorize categorical and binary outcomes. For non-parametric testing on unpaired continuous data, the Wilcoxon rank sum test will be used. All outcomes will be adjusted for baseline serum 25(OH)D levels, and for mean serum levels achieved at weeks 16 and 24.

Missing data will be imputed as the mean of the preceding and following measurements. Only patients completing at least 4 months of full participation in the study or experiencing a relapse at any time in the study will be included in the final analysis. Non-adherent participants, defined as those with an increase in serum level of 25(OH)D of less than 50 nmol/l from baseline, will be excluded from the final analysis.

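### The averaging rule for missing data sets an imputed participant's week-16 immune change to half the week-24 change, and gives no value at week 24

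*Protocol article*

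**What the plan says.** Statistical methods states a single rule with no exception by outcome or visit: "Missing data will be imputed as the mean of the preceding and following measurements".

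The measurement times are set elsewhere in the article:

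- **Immune measures (primary).** Study visits and outcome parameters: "Immunologic analysis will be carried out at baseline, and at weeks 16 and 24". Study endpoints makes the comparison "at weeks 16 and 24 compared with baseline".
- **MRI (secondary).** Figure 1 legend: "Magnetic resonance imaging will be carried out at baseline and week 24 in the CIS population only".
- **25(OH)D.** Study visits and outcome parameters: "Serum vitamin D levels and parathormone levels will be assessed at baseline, and at weeks 4, 8, 12, 16 and 24".
- **After week 24.** The same section says only that "a safety visit at week 28 will also be arranged". No immune test, MRI or 25(OH)D measurement is listed for it.

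Two further statements bear on who can have missing values. Statistical methods limits the final analysis to "Only patients completing at least 4 months of full participation in the study or experiencing a relapse at any time in the study", and then removes non-adherent participants. Sample size says: "Recruiting 39 healthy controls and 45 patients with CIS will allow for a drop-out rate of 20% and 30% respectively".

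**The concern.** Averaging the two neighbouring values is a form of interpolation. It is reasonable when a gap lies between two closely spaced measurements taken under the same conditions. The primary outcome here is not like that. The only immune measurement before week 16 is the untreated baseline, so the rule mixes a pre-treatment value into an on-treatment outcome. It also presents half of the week-24 result as a separate week-16 observation.

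At the last measurement, the rule has nothing to average. That is also where an analysed participant who leaves late would have the gap.

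The stakes are a week-16 comparison that can be pulled towards no effect with too little spread, and a week-24 comparison for which the stated rule gives no answer. Sample size plans for about 10 evaluable participants per arm, so one or two such values matter.

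**Working it through.** **Inputs.** Immune measures at weeks 0, 16 and 24, MRI at weeks 0 and 24, and 25(OH)D at weeks 0, 4, 8, 12, 16 and 24 (Study visits and outcome parameters; Figure 1 legend). At least 10 per group and drop-out allowances of 20% and 30% (Sample size). The share m of an arm's week-16 values that would be imputed is not given; 10% to 30% is assumed. With 10 evaluable participants that is 1, 2 or 3 people.

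**1. The plan's own figures.** 10/(1 − 0.20) = 12.5, rounded up to 13; 13 × 3 = 39. 10/(1 − 0.30) = 14.3, rounded up to 15; 15 × 3 = 45. Both totals reproduce. This arithmetic treats drop-outs as lost to the analysis (13 × 0.8 = 10.4 and 15 × 0.7 = 10.5 remain). It says nothing about how many analysed participants lack a given visit.

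**2. Where the rule gives a value.**

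| Outcome | Baseline | Week 16 | Week 24 |
|---|---|---|---|
| Immune | no preceding value | mean of baseline and week 24 | no following value |
| MRI | no preceding study scan | not measured | no following scan |
| 25(OH)D | no preceding value | mean of weeks 12 and 24 | no following value |

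For the immune outcomes the rule works at one of three visits, and for MRI at neither of two.

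**3. What it does at week 16.** Let Y0, Y16 and Y24 be a participant's immune values. If Y16 is missing:

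imputed change = (Y0 + Y24)/2 − Y0 = (Y24 − Y0)/2.

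This is exactly half of that participant's week-24 change, so its SD is also half. A simulation with unit variances, equal correlations and a true change of 1.00 at both visits gave a mean imputed change of 0.50. The SDs were 0.59, 0.50 and 0.39, against 1.18, 1.00 and 0.77 for the real change, at correlations 0.3, 0.5 and 0.7.

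**4. How this compares with the true week-16 effect.** If the week-24 effect is r times the week-16 effect, the imputed value carries r/2 of the week-16 effect: 25%, 50%, 75% and 100% for r = 0.5, 1, 1.5 and 2.

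**5. Arm level, taking r = 1 and correlation 0.5.** The expected mean is multiplied by 1 − m/2.

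| m | Mean effect, formula | Mean, simulated | SD of change, simulated (true 1.00) |
|---|---|---|---|
| 10% | 0.95 | 0.949 | 0.972 |
| 20% | 0.90 | 0.899 | 0.944 |
| 30% | 0.85 | 0.851 | 0.913 |

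In the plan's units, a true IL-17 change of 44.5 (anti-CD3, Sample size) would appear as 44.5 × 0.95 = 42.3, 44.5 × 0.90 = 40.1 or 44.5 × 0.85 = 37.8. The spread shrinks too, so the loss in signal-to-noise is smaller than the loss in the mean, but only because the filled-in values are treated as real.

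**6. Who lacks week 24.** Four months is about 4/12 × 52 = 17 weeks. A non-relapsing participant who leaves earlier is excluded. One who completes 4 months and then leaves will usually have week 16 and lack week 24, where the rule fails. A relapsing patient who leaves before week 16 stays in the analysis and lacks both visits. With week 24 missing, the rule cannot fill week 16 either.

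**The case against.** The case on the other side is substantial in places.

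- **Isolated week-16 gaps should be uncommon.** The rule can fill week 16 only for someone who misses that sample and returns at week 24. A drop-out does not. The 4-month participation criterion also falls at about week 16, and cells are stored until all three samples are in. This stands: 10% to 30% imputed is an assumed range, and the true share could be lower.
- **The shrinkage is conditional.** A reader might infer that the rule halves the trial's week-16 effect. It does not. Only the imputed participants are affected, and their value is half of the true week-16 effect only if effects at the two visits are equal. If the week-24 effect were twice the week-16 effect, the mean would not shrink at all.
- **The planned tests are rank-based.** Halving a change keeps its sign, so a sign test would use the sign of the week-24 change whatever the shrinkage. Signed-rank and rank-sum tests can be affected, but the mean and SD figures do not measure by how much.
- **The drop-out figures are not week-24 missingness.** A reader might take 20% to 30% of week-24 values to be missing. Sample size gives an overall allowance, and Rescue therapy advises relapsing patients to continue study visits. The article gives no number for analysed participants without week 24.
- **An analysis plan may deal with the last visit.** It may, and it is not shown. But the article does not leave the matter open. It states one rule for all missing data, and that rule does not fit the schedule.

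These points limit the size of the harm. They do not make the rule workable at week 24 or make a pre-treatment value a fair stand-in at week 16. The exploratory label does not change this either.

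**Conclusion.** The point holds in two parts that follow from the article alone: an imputed week-16 immune change is exactly half of the same participant's week-24 change, with half its SD; and the rule gives no value for a missing week-24 immune, MRI or 25(OH)D measurement.

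The arm-level reduction of 5%, 10% or 15% in the mean week-16 effect is less certain. It rests on equal true effects at weeks 16 and 24 and on an assumed 10%, 20% or 30% of week-16 values imputed. That gaps among analysed participants would fall mainly at week 24 is a sound inference from the 4-month criterion, but not a stated figure. The article supports neither a halving of the whole week-16 effect nor a 20% to 30% loss at week 24.

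**What to change.** Delete the averaging rule for the immune and MRI outcomes. Analyse the observed week-16 and week-24 values without imputation, using the planned rank-based tests on observed changes from baseline. For missing binary outcomes, such as freedom from disease activity, add a best/worst-case sensitivity check. If averaging is kept for 25(OH)D, limit it to visits with a scheduled measurement on each side, and state that week 24 is not imputed.

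A repeated-measures mixed model using all observed visits may be added as a supportive analysis. Making it the main analysis would replace the planned rank-based tests with a parametric model at about 10 to 15 per arm. That is a debatable choice and is not needed to cure this defect.

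The cost is slightly fewer values at week 16 and a little more analysis work. No visits, samples or participants are added.

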## Discussion

Supplemental vitamin D appears to have potential as a therapeutic agent for MS; what is less clear is the optimal dose of vitamin D needed to effect change within the immune system. Our study is designed to address this question, and to add to the growing evidence of the safety and tolerability of high-dose vitamin D supplementation. As this is a phase II randomized, placebo-controlled trial with two distinct study groups and is adequately powered to meet the primary endpoint, it should be considered a high-quality trial aiming to provide class II evidence of the primary endpoint.

Existing guidelines on vitamin D supplementation are conservative, and refer mainly to bone health [33], with 4,000 IU considered the upper limit of tolerability, despite the fact that sun exposure can provide an adult with up to 20,000 IU per day [34]. Older adults are now advised to sustain 25(OH) D concentrations of greater than 75 nmol/l for optimal bone health and, in order to achieve that, they need to consume approximately 4,000 IU/day of vitamin D [18,35]. Levels greater than 100 nmol/l are needed to ensure that patients are receiving adequate immunomodulating doses of vitamin D. Based on previous dosing studies [18], the maximum serum 25(OH)D level expected with a daily dose of 10,000 IU is approximately 250 nmol/l, making both treatment doses safe and tolerable.

The availability of DMT and the earlier recognition and diagnosis of MS have a significant effect on trial design for the evaluation of new drugs, and this also raises ethical concerns. Most would feel that placebo-controlled studies of the RRMS population are unethical. This results in the need for large multicenter trials to achieve adequate numbers to power the study over longer time periods to assess for clinical endpoints. Thus, costs are generally prohibitive and really limits these studies to large pharmaceutical companies.

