In Ireland, the UK, Australia, and New Zealand, patients with CIS are treated conservatively until there is evidence, on clinical or MRI grounds, of dissemination in time. Patients with CIS form a distinct population with a well-established natural history, who are not exposed to immunomodulatory therapy. Given the standard practice in Ireland, there is no ethical concern with regard to watchful withholding of treatment. Should patients convert to RRMS during the trial, they will be offered standard DMT. This study should add to the growing evidence of the immunomodulatory effects of high-dose supplemental vitamin D in demyelinating disease. We hope to show that vitamin D is a safe and effective therapy for patients with CIS.

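### The only analysis set stated conditions on 4 months of participation and on a 25(OH)D rise, with no exemption for the trial's stated safety and tolerability aim

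*Protocol article*

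**What the plan says.** **The aim.** The Discussion states that the study is meant "to add to the growing evidence of the safety and tolerability of high-dose vitamin D supplementation", and closes with "We hope to show that vitamin D is a safe and effective therapy for patients with CIS". Safety is not among the primary or secondary endpoints listed under Study endpoints.

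**The data.** Under Study visits and outcome parameters, biochemistry including serum calcium is taken at every visit. Visits are 4-weekly to week 24, with a further safety visit at week 28.

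**The analysis set.** Statistical methods describes one set, called the final analysis, through two rules:

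- Completion: "Only patients completing at least 4 months of full participation in the study", continuing "or experiencing a relapse at any time in the study will be included in the final analysis".
- Biochemical adherence: for the group it calls non-adherent, the text reads "defined as those with an increase in serum level of 25(OH)D of less than 50 nmol/l from baseline, will be excluded from the final analysis".

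Neither rule is limited to the immunologic or efficacy outcomes. The first speaks of patients and the second of participants.

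**Expected loss.** Sample size says: "Recruiting 39 healthy controls and 45 patients with CIS will allow for a drop-out rate of 20% and 30% respectively".

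**The concern.** Tolerability is largely a question about people who stop. A set that requires about 16 of the 24 treatment weeks selects those who could take the oil. The completion rule makes one exception, for relapse, so the authors recognised that some early leavers carry outcome information. There is no matching exception for adverse events or intolerance. A participant who stopped at week 8 for raised calcium and had no relapse would be outside the set.

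The 25(OH)D rule adds two problems. Someone who cut back on the oil because of side effects could be classed as non-adherent and removed. And, as worded, it is not confined to the active arms. Placebo participants receive no vitamin D from the study oil, so most would not be expected to rise by 50 nmol/l. Taken literally, the rule removes most of the comparator against which adverse event rates would be judged.

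Arms are 13 or 15 people per population, so a handful of early stops could decide what the trial reports about tolerability.

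**Working it through.** **1. The plan's own figures.** Inputs from Sample size: 10 evaluable per arm, three arms per population, drop-out 20% (controls) and 30% (CIS).

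- Controls: 10 / (1 − 0.20) = 12.5, rounded up to 13; 13 × 3 = 39.
- CIS: 10 / (1 − 0.30) = 14.3, rounded up to 15; 15 × 3 = 45.

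Both totals reproduce. The article states no safety figure, so none can be reproduced.

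**2. Size of the expected loss.**

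- Planned drop-out: 39 × 0.20 + 45 × 0.30 = 7.8 + 13.5 = 21.3 of 84, or 25%.
- Per dose over both populations: 13 + 15 = 28 randomised; 13 × 0.8 + 15 × 0.7 = 20.9, about 21, remaining.

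The article does not say when drop-out occurs. The figure of 21 is therefore what is left if all planned drop-out falls before 4 months without a relapse.

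**3. What the completion rule does to a tolerability rate.** The counts of early stops are assumptions; the documents give none. Each row assumes that everyone randomised took at least one dose, that all the stops fall before 4 months without a relapse, and that nobody else is excluded. The control and pooled rows also assume that the rule covers controls. Intervals are exact (Clopper-Pearson) two-sided 95%.

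| Group | Assumed early stops | All treated | Set as written |
|---|---|---|---|
| CIS arm, 15 | 1 | 6.7% (0.2 to 31.9) | 0/14, upper limit 23.2% |
| CIS arm, 15 | 3 | 20.0% (4.3 to 48.1) | 0/12, upper limit 26.5% |
| CIS arm, 15 | 4 | 26.7% (7.8 to 55.1) | 0/11, upper limit 28.5% |
| Control arm, 13 | 1 | 7.7% (0.2 to 36.0) | 0/12, upper limit 26.5% |
| Control arm, 13 | 2 | 15.4% (1.9 to 45.4) | 0/11, upper limit 28.5% |
| One dose, pooled, 28 | 3 | 10.7% (2.3 to 28.2) | 0/25, upper limit 13.7% |
| One dose, pooled, 28 | 7 | 25.0% (10.7 to 44.9) | 0/21, upper limit 16.1% |

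The fall to zero is by construction, because the rule removes exactly the cases being counted. The table shows how the rule behaves and is not evidence that such stops will occur.

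**4. Precision when no events are seen.** The one-sided 95% upper limit for zero events in n is 1 − 0.05^(1/n).

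- n = 28: 1 − 0.05^(1/28) = 10.1%.
- n = 21: 1 − 0.05^(1/21) = 13.3%.

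Even with no events and everyone kept, a true rate of about 10% on a dose cannot be excluded. The restricted set widens this further.

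**5. The 25(OH)D rule.** The Background cites a rise of 150 nmol/l over 12 weeks on 10,000 IU daily. The 50 nmol/l threshold is one third of that (50 / 150). The placebo oil contains no vitamin D. That most placebo participants would fall below the threshold is an expectation, not a figure in the article; season or permitted supplements could move some above it.

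**The case against.** The strongest reply is that the rule was never meant for safety. It sits among the test choices, the 25(OH)D adjustment and the imputation rule. Four months is close to week 16, the first post-baseline immunologic sample, and the exception is for an efficacy event. Safety has its own visits and measurements, and an all-treated safety set is commonly left to a full protocol or SAP that is not shown. The text available also lacks a short part after Statistical methods. All of this stands, and the absence of a safety set is not the point made here. What remains is that the rule is written with the word only, governs an unqualified final analysis, and sits in an article that states a safety aim.

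Three stronger readings are tempting, and the documents do not support them:

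- A reader might infer that intolerant participants will disappear from the safety conclusion. No sentence says that safety is summarised in this set, and early leavers with a relapse are kept.
- A reader might take "making both treatment doses safe and tolerable" as a conclusion that the trial commits itself to. That sentence rests on earlier dosing studies and cannot be biased by this trial's analysis set. The trial's own statements are an aim and a hope.
- A reader might infer a bias in favour of the higher dose. That needs early withdrawal to be dose-related, for which no figure is given. The Background reports no adverse events or hypercalcemia in a cited trial with a mean dose of 14,000 IU per day.

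It is also fair to say that the reach of the completion rule to healthy controls is unclear, so the pooled figures depend on one reading of it.

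**Conclusion.** The concern holds in conditional form. If the completion and 25(OH)D rules are applied as written to the stated safety and tolerability aim, they exclude those who stop early for intolerance without a relapse, and they exclude most placebo participants. On assumed counts, 10.7% (3/28) on a dose would read as 0%, and 20% (3/15) in a CIS arm would read as 0/12. These figures rest on the assumptions set out with the table. Whether the rules will be used for safety cannot be settled from the article. The wording should be corrected: the ambiguity is easy to remove, and with arms this small the choice of set could change the tolerability result.

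**What to change.** Add to Statistical methods a sentence stating that neither the 4-month rule nor the 25(OH)D rule applies to safety and tolerability. Then state that hypercalcemia, other laboratory abnormalities, adverse events, and withdrawals with their reasons are reported by arm in all participants, patients and healthy controls, who took at least one dose, from first dose through the week 28 visit. Give each rate with an exact confidence interval, and word the safety conclusion to that precision. In the same edit, say whether the 4-month rule covers healthy controls.

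The cost is a few lines of text and one table from data already collected at the planned visits. The downside is a more cautious safety statement: even zero events in 28 leaves an upper limit of about 10%.

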### Rescue therapy

In the event of a relapse, the patient will undergo appropriate investigations and be commenced on steroid therapy if appropriate. As these patients will then meet the McDonald 2010 criteria [31] for diagnosis of MS, they will be offered treatment in line with the current recommendations for first-line treatment of RRMS. They will be advised to continue study visits for the duration of the trial.

Participants with CIS whose MRI scans show new lesions at the end of the study period (24 weeks) meeting the McDonald 2010 criteria [31] for MS will also be offered first-line therapy for RRMS, as is standard practice in our institution.

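### The final analysis set keeps patients with CIS who leave early only if they relapsed, which distorts relapse results within each arm and, when drop-out is unequal or informative, the comparison with placebo

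*Protocol article*

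**What the plan says.** The Statistical methods section of the protocol article defines one final analysis. It admits two kinds of patient: "Only patients completing at least 4 months of full participation in the study or experiencing a relapse at any time in the study". The next sentence adds a second exclusion: "Non-adherent participants, defined as those with an increase in serum level of 25(OH)D of less than 50 nmol/l from baseline, will be excluded". It makes no exception for patients who relapsed. The article gives no other analysis set for the relapse endpoints.

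Under Study endpoints, the secondary outcomes in CIS include "relapse occurrence, calculated as the annualized relapse rate (ARR), the percentage of patients who are relapse-free, and time to first relapse", each compared with placebo. Relapse also enters the composite outcome, the "percentage of treated patients with CIS who are free from any evidence of disease (clinical and MRI) activity".

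Follow-up is fixed: "Study duration is 24 weeks with immunologic testing (primary endpoint) of all study participants at baseline, week 16, and week 24". Under Rescue therapy, patients who relapse stay under observation: "They will be advised to continue study visits for the duration of the trial". The Sample size section states: "Recruiting 39 healthy controls and 45 patients with CIS will allow for a drop-out rate of 20% and 30% respectively".

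**The concern.** Take two patients with CIS who both leave at week 10, one after a relapse and one without. The first is analysed and the second is not. The only difference between them is the outcome being measured.

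So every observed relapse is counted (unless the serum-level rule removes it), while part of the relapse-free time is deleted. A patient without a relapse has to remain for 4 months to be counted; a patient with one does not.

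This is a rule that the article states, not a detail left to a later document. If it is followed, relapse results in each arm are shifted in a known direction. If more patients leave one arm than another, or leave for reasons linked to relapse, the shift differs by arm and can be mistaken for a treatment effect.

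**Working it through.** **The plan's own figure.** The Sample size section concludes that "at least 10 subjects should be included in each group". Inflating 10 per arm for drop-out:

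- Controls: 10/(1 − 0.20) = 12.5, rounded up to 13; 13 × 3 = 39.
- CIS: 10/(1 − 0.30) = 14.3, rounded up to 15; 15 × 3 = 45.

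Both stated totals reproduce. The drop-out allowance is not at fault; the rule about who is analysed is.

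**Inputs.** From the article: 24 weeks of follow-up and a 30% drop-out allowance in CIS. Assumed, because the article does not give them: a 24-week risk of first relapse p between 10% and 40%, constant hazards, drop-out independent of relapse, and 4 months = week 16. Only first relapses are modelled, with a year of 52 weeks.

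**Formulas.** λ = −ln(1 − p)/24 (relapse), δ = −ln(1 − q)/24 (drop-out), s = λ + δ.

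- Share removed by the rule: (δ/s)(1 − e^(−16s))
- Share with an observed relapse: (λ/s)(1 − e^(−24s))
- Weeks at risk per patient, all randomised: (1 − e^(−24s))/s
- Weeks removed per randomised patient: (δ/s)[(1 − e^(−16s))/s − 16e^(−16s)]

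**p = 20%, q = 30%.** λ = 0.00930, δ = 0.01486, s = 0.02416.

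- Removed: 0.615 × 0.321 = 19.7% of randomised patients, none with an observed relapse.
- Observed relapse: 0.385 × 0.44 = 16.9%.
- Weeks at risk: 0.44/0.02416 = 18.21. Weeks removed: 0.615 × 2.40 = 1.48. Weeks left: 16.74.
- Rate, all randomised: 52 × 0.1693/18.21 = 0.484. Rate under the rule: 52 × 0.1693/16.74 = 0.526, a factor of 1.09.
- Kaplan-Meier under the rule: relapse by week 16 is 0.385 × 0.321 = 0.1234, over 0.8028 retained = 0.1537. Relapse-free at week 24 is 0.8463 × e^(−8λ) = 0.8463 × 0.928 = 0.786. Risk is 21.4% against a true 20%.

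**Range at 30% drop-out.**

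| True 24-week risk | Rate, all randomised | Rate under the rule | Kaplan-Meier risk under the rule | Removed |
|---|---|---|---|---|
| 10% | 0.228 | 0.248 | 10.8% | 20.5% |
| 20% | 0.484 | 0.526 | 21.4% | 19.7% |
| 30% | 0.773 | 0.841 | 31.9% | 18.9% |
| 40% | 1.107 | 1.205 | 42.3% | 18.1% |

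The rate is overstated by about 2% at 10% drop-out, 5% at 20% and 9% at 30%, almost regardless of the relapse risk.

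**Between arms.**

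- Equal 30% drop-out, true risks 40% v 20%: rate ratio 0.484/1.107 = 0.437 in all randomised and 0.526/1.205 = 0.437 under the rule.
- No true effect (20% risk), drop-out 20% v 40%: 0.509/0.547 = 0.93.
- No true effect (30% risk), drop-out 10% v 40%: 0.792 v 0.875, so the arm with more drop-out appears about 1.10 times as high.

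**The case against.** The strongest reply is that these endpoints are comparisons with placebo, and with equal, non-informative drop-out the rate ratio does not move. That stands. A reader might infer from the rule that every treatment comparison is biased; the article does not support this, because it says nothing about drop-out differing by arm or being linked to relapse. Nor does it ensure the opposite, and with 15 patients per arm, 20% v 40% is 3 v 6 leavers.

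The bias is also small beside the noise. With an assumed three relapses per arm (20% of 15), the standard error of the log rate ratio is √(1/3 + 1/3) = 0.82, while ln 0.93 is −0.07. This also stands, and it lowers the priority.

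Four other stronger readings should be set aside:

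- **Early leavers are lost only if relapse-free.** This is true of the one sentence. The serum-level exclusion that follows can remove relapsers too.
- **The crude proportion in all randomised patients is the right benchmark.** It is not, because it treats everyone who left as relapse-free to week 24. In the worked case it gives 16.9%, further from the true 20% than the 21.1% (16.93/80.28) under the rule. The fair comparator is the censored estimate.
- **4 months means calendar months, so people who gave the week-16 sample are discarded.** Visits and dispensing run every 4 weeks and immune sampling falls at week 16, so week 16 is the natural reading.
- **The primary immune comparison is damaged to the same degree.** Anyone leaving before week 16 has no immune sample after baseline, so this rule removes little usable primary data. In healthy controls, for whom relapse is not an endpoint, selection on relapse does not arise.

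**Conclusion.** The point holds for the relapse endpoints in CIS. The rule selects on the outcome. For the annualised rate the direction needs no modelling: patients with no events and positive follow-up are removed, so the rate rises. Removing them also shrinks the early risk sets without removing any event, so the Kaplan-Meier relapse curve rises and time to first relapse shortens. The relapse-free percentage was understated in every case computed. The composite outcome contains relapse and is exposed to the same selection; its size was not calculated.

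At the 30% drop-out allowed for, the rate is about 9% too high and, at a 20% risk, the Kaplan-Meier risk is 1.4 percentage points too high. The comparison with placebo is affected when drop-out differs by arm or is informative: a false ratio of about 0.93 at 20% v 40%. These sizes rest on assumed relapse risks, constant hazards, independent drop-out, first relapses only, and a week-16 cut. Drop-out concentrated earlier or later, or repeat relapses in patients who continue visits, would change them.

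The rule should be corrected, but it is not critical: the affected endpoints are secondary, in an exploratory trial sized on immune measures.

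**What to change.** Replace the inclusion sentence for the relapse endpoints with the following:

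- **Set:** all randomised patients with CIS, by assigned arm. The serum-level exclusion would then not apply to this set either; whether that rule is sound is a separate question.
- **Annualised relapse rate:** all events over all person-time, from a rate model with log follow-up time as offset.
- **Time to first relapse and percentage relapse-free:** Kaplan-Meier, censoring at last contact.
- **Immune endpoints:** every available week-16 or week-24 sample, without reference to relapse status.
- **Sensitivity analysis:** a completer set may be kept if it is defined by a stated study week and not by relapse.

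Report drop-out by arm, with timing, so that a reader can judge whether the comparison is exposed. The cost is a change of wording made before unblinding. It needs no new patients, visits or measurements, because the follow-up of early leavers is already recorded up to the time they leave.
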